## Abstract

**Background:**

Asthma is one of the most common respiratory ailments worldwide. Despite broad understanding of the illness and of the available therapeutic options for it, patients with serious asthma suffer poor monitoring of their illness in 50% of cases.

**Aim:**

To assess the impact of the implementation of a mobile application (ESTOI) to control asthma in patients diagnosed with the illness, their adherence to treatment, and their perceived quality of life.

**Methodology:**

Randomized clinical trial with 52 weeks’ follow-up of patients with asthma seen in a specialized hospital for their treatment in Spain. Some 108 included patients will be divided into two groups. The intervention group will undergo more exhaustive follow-up than normal, including access to the ESTOI application, which will have various categories of attention: control of symptoms, health recommendations, current treatment and personalized action plan, PEF record, nutritional plan, and chat access with a medical team. The asthma control questionnaire ACT is the main assessment variable. Other variables to be studied include an adherence test for the use of inhalers (TAI), the number of exacerbations, maximum exhalation flow, exhaled nitric oxide test, hospital anxiety and depression scale, asthma quality-of-life questionnaire, forced spirometry parameters (FVC, FEV1, and PBD), and analytic parameters (eosinophilia and IGE). The data will be collected during outpatient visits.

**Trial registration:**

This trial has registered at ClinicalTrials.gov (Identifier: NCT06116292).

## Background

Asthma is one of the most common respiratory ailments worldwide [1]. It was estimated in 2019 that asthma affected 262 million people and caused 461,000 deaths [2]. In recent decades there has been a significant increase in the prevalence of asthma worldwide. According to the *Global Burden of Disease* study in 2015, between 1990 and 2015 the prevalence of the illness increased by 12% [3].

Asthma is manifested by bronchial hyper-response and variable obstruction of the air flow, which may be partially or totally reversible [1]. Its main symptoms are cough, wheezing, shortness of breath, pressure in the chest, and a limitation in the flow of expired air [4]. As it is a chronic illness, the aim in treatment is to reach and maintain control of the pathology and prevent future risk, especially of exacerbation, which may be life-threatening to the patient [1, 4].

Despite widespread knowledge of the illness and of the available therapeutic options, asthmatic patients show poor control of the illness in 50% of cases [5]. Because of this, symptoms may be persistent and may include constant exacerbations that present a great future risk [6, 7]. In part, poor control of the illness may be due to a lack of adherence and therapeutic compliance, to environmental exposures, and to poor control of comorbidities that directly affect asthma such as obesity, chronic sinusitis, allergic rhinitis, gastro-esophageal reflux, anxiety, and depression [1, 8].

In recent years there has been an increase in the demand for telemedicine in combination with or as an alternative to face-to-face clinical care [1]. This has led to the creation and management of new models of patient care [4, 9]. Follow-up and monitoring control of patients with asthma in accordance with evidence-based recommendations must include in assessment a monitoring of symptoms and acute incidents, continuous assessment of causative agents and comorbidities that have an impact on control of the illness, changes in pulmonary function, the side effects of treatment, and, finally, the ability of patients to carry out personalized and predesigned action plans [1, 4, 9].

Recent studies have highlighted the great potential of mobile applications to improve self-care of patients with asthma, as an efficient way to offer and share information, in addition to being of low cost and easily accessible to the population [10–12]. Despite this, owing to the diversity of interventions and their results in recent years, there is a lack of consensus regarding the type of intervention best suited to asthmatic patients and the tools needed to improve control of their illness [10–15].

For this reason, the present project has set out to develop and use a telemedicine tool for global management of patients with asthma, in order to improve adherence to treatment, increase control of the illness, empower the patients, personalize their care, and increase the efficiency of the circuit, thereby improving the quality of care.

## Aim

The aim of the present study is to assess the impact of the implementation of a mobile application (ESTOI) to control asthma in patients diagnosed with the illness, their adherence to treatment, and their perceived quality of life.

## Method

### Design

A simple-blind randomized clinical trial will be carried out, with 52 weeks of follow-up of patients with asthma. The study will have two arms: the control cohort will receive normal care, while the intervention group will additionally have access to the mobile application (ESTOI).

### Setting and subjects

The study will be carried out in the pneumology service of the Bellvitge University Hospital in Barcelona, during the period 2023–2025. The participants will be asthmatic patients seen for the first time in the hospital out-patient clinic who fulfill the following selection criteria (Table 1).

**Table 1 Tab1:** Key inclusion, exclusion, and withdrawal criteria

Key inclusion criteria	
• Age ≥ 18 years with a diagnosis of asthma based on GEMA 5.2, 2022 [1] • Patients seen in the pulmonology service of the center. • Patients who have not previously received asthma education. • Capable of giving signed informed consent.	
Key exclusion criteria	
• Patient does not have a mobile device with Android or IOS system. • Lack of minimum technological knowledge for the use of the application (ESTOI). • People participating or have participated in a clinical trial in the last 6 months. • Patients diagnosed with other respiratory diseases except for obstructive sleep apnea (OSA), Asthma-COPD overlap syndrome (ACOS). • Patient with palliative or severe chronic illness that limits life expectancy.	
Key withdrawal criteria	
• Voluntary withdrawal from the study by the patient. • Lost to follow-up. • Death of the patient.	

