### Calculation of the sample

In order to calculate the sample size, a screening of 60 patients seen in the pneumology unit of the center was made with the ACT questionnaire, in order to learn the degree of current control of the asthma of those patients.

With a CI of 95% and a standard deviation of 4.95, the average ACT score of the patients seen in our center was 18.43 ± 1.25. The calculation of the sample size was based upon the established aims. We used the Granmo 7.12 program for two independent averages, accepting an alpha risk of 0.05 and a beta risk of 0.2 in bilateral contrast. Some 54 subjects were determined to be needed for each group in order to detect a difference equal to or greater than 3 units in the ACT questionnaire [16, 17]. We assumed a common standard deviation of 4.95 (obtained by screening in our center) and calculated a rate of loss in follow-up of 20%.

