**Exacerbation**	In asthma an exacerbation is considered a worsening of asthma symptoms that requires medical intervention and has at least 1 of the following 3 elements listed below for at least 2 consecutive days: Worsening of asthma signs/symptoms (dyspnea, wheezing, nocturnal awakenings, or chest tightness), increased use of rescue medication or deterioration of lung function [1].	CG at each visit (v1, v2, v3) IG once a month (using the ESTOI app) and at each visit of the study (V1, V2, V3)
**Peak Expiratory Flow (PEF)**	PEF is the highest airflow achieved in a forced expiration after an also forced inspiration, measured using a Peak Flow Meter. It is used as a predictor of airway obstruction [23].	Both groups (IG and CG) once a week (using the ESTOI app in case of IG) and at each visit of the study (V1, V2, V3)
**Forced vital capacity (FVC)**	FVC is the total volume of air that can be exhaled during a maximum effort of forced expiration without a time limit [24].	Both groups (IG and CG) at each visit (V1, V2, V3)
**Forced expiratory volume in one second (FEV1)**	FEV1 is the volume of air exhaled in the first second under force after a maximal inhalation [24].	Both groups (IG and CG) at each visit (V1, V2, V3)
**Bronchodilator Responsiveness (BDR)**	BDR determines the degree of airflow improvement after the administration of a Beta-2 adrenergic agonist. The test is considered positive when there is an increase from baseline values of FEV1 by at least 12% and 200 mL [24].	Both groups (IG and CG) at each visit (V1, V2, V3)
**Fractional exhaled nitric oxide (FeNO)**	FeNO is a useful and noninvasive biomarker for eosinophilic airway inflammation, particularly in asthma [25].	Both groups (IG and CG) at each visit (V1, V2, V3)

*CG* Control group, *IG* Intervention group

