A nurse trained in telemedicine will be in charge of the management and monitoring of the patients using the application. The nurse will also be responsible for making appointments, reviewing the clinical records of all the patients included in the study, and managing the case report and informed consent forms. The nurse specialized in asthma will be responsible for administering the questionnaires, collecting the case report form data, and the carrying out of the blood tests and pulmonary function testing.

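### Exacerbations are captured at three visits in controls but also monthly by app in the intervention group, and no route is named for patients who stop attending, so patients who leave contribute less in the control arm

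*Protocol article*

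**What the plan says.** All references are to the protocol article.

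- **Setting and subjects, Table 1.** The withdrawal criteria are "Voluntary withdrawal from the study by the patient", loss to follow-up and death. What happens to outcome collection afterwards is not described.
- **Abstract, Methodology.** "The data will be collected during outpatient visits".
- **Variables, Table 2.** An exacerbation is "a worsening of asthma symptoms that requires medical intervention", with further conditions. Controls are assessed for it at V1, V2 and V3. The intervention group is assessed at the same visits and also monthly through the app. The visits fall at baseline, 6 and 12 months.
- **Procedure and instruments.** The telemedicine nurse is responsible for "reviewing the clinical records of all the patients included in the study". The purpose and timing of that review are not stated, and Table 2 does not name it as a source for exacerbations.
- **Limitations.** The electronic medication history will be reviewed, for adherence. The authors accept that patients who leave early would skew the results.
- **Calculation of the sample.** The plan "calculated a rate of loss in follow-up of 20"%, with no split by arm or by reason.

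**The concern.** The collection schedule for this outcome differs by arm, and the difference matters most for patients who leave. A control who stops attending in month 5 has given only the baseline record, so the months already spent in the study yield nothing. An app patient who stops at the same time can have sent five monthly reports. The opportunity to record an event therefore depends on the allocated arm, and a comparison of exacerbation numbers partly measures that opportunity.

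The loss looks avoidable. By the plan's own definition an exacerbation needs medical intervention, so it will usually leave a trace in a clinical record, and a nurse already reads the records of every included patient. An analysis cannot restore events that were never collected, so this has to be settled in the collection schedule.

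**Working it through.** **1. The plan's own figure.** The inputs, from Calculation of the sample, are "accepting an alpha risk of 0.05 and a beta risk of 0.2 in bilateral contrast", a target to "detect a difference equal to or greater than 3 units in the ACT questionnaire", and "We assumed a common standard deviation of 4.95".

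n per group = 2 × [4.95 × (1.960 + 0.842) / 3]² = 42.7, rounded up to 43.

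Allowing for 20% loss: 43 / 0.80 = 53.75, rounded up to 54 per group, or 108 in total. The stated size reproduces. Expected loss is 54 − 43 = 11 per arm, 22 in all.

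**2. Person-months captured, by arm.** These assumptions are not in the documents: leaving times are uniform over 12 months, 20% are lost in each arm, the event rate is constant with no true effect, each visit captures everything since the previous one, and no other source is used.

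- Full follow-up per arm: 54 × 12 = 648 person-months.
- Completers in either arm: 43 × 12 = 516.
- Lost controls: half leave before V2 and contribute 0 months, and half leave after V2 and contribute 6. The mean is 3, so 11 × 3 = 33.
- Lost app patients: complete monthly reports run evenly from 0 to 11. The mean is 5.5, so 11 × 5.5 = 60.5.

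| | Control | App |
|---|---|---|
| Captured person-months | 516 + 33 = 549 | 516 + 60.5 = 576.5 |
| Share of 648 | 85% | 89% |

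Apparent rate ratio from raw counts, app to control: 576.5 / 549 = 1.05. The truth under these assumptions is 1.00.

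**3. Sensitivity to the loss rate d, equal in both arms.** Control share = 1 − d + 0.25d. App share = 1 − d + (5.5/12)d.

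| d | Control | App | Ratio |
|---|---|---|---|
| 10% | 0.925 | 0.946 | 1.02 |
| 20% | 0.850 | 0.892 | 1.05 |
| 30% | 0.775 | 0.838 | 1.08 |

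**4. Time after leaving.** With uniform leaving, a share d/2 of person-time falls after departure. At 20% loss this is 10% in both arms, so it creates no imbalance by itself. Unequal loss would: 10% against 30% gives 5% against 15%. The documents give no such split.

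**The case against.** Several stronger readings are tempting, and the documents do not support them.

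- *All data come from visits alone.* The abstract does not say so, and the app supplies monthly reports in one arm. The record review and the medication history are further sources.
- *Events after leaving are discarded.* The article never says that collection stops or that records go unsearched. Handling after withdrawal is commonly left to the full protocol, the analysis plan or the consent form, and silence in a condensed article is not a finding.
- *Events after leaving are lost unequally by arm.* This needs unequal or differently selected loss. Suppose 30% of each arm have 2 events a year, the rest have 1, and every lost patient is from the first group. The completers' mean is then (0.10 × 2 + 0.70)/0.80 = 1.125 in both arms at 20% loss, a ratio of 1.00. Only an assumed split moves it: 15% app loss against 25% control loss gives 1.176/1.067 = 1.10, and the reverse gives 0.91. Both cases are extreme, because between half and five-sixths of all high-rate patients would have to leave.
- *Deaths hide exacerbations.* No exacerbation follows a death, and nothing prevents a fatal one from being recorded as an event.

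It can also be said that voluntary withdrawal is worded as leaving the study, so further use of records depends on consent. The existing review might also already be meant to supply exacerbations. Finally, an analysis of rates that uses each patient's captured time as the denominator would return the ratio in step 2 to 1.00 under the same assumptions.

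Much of this stands, and it narrows the point. It does not remove the difference in schedule that Table 2 states, or the fact that the review is not named there. The rate analysis works only if leaving is unrelated to exacerbation risk, which the Limitations section itself doubts.

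**Conclusion.** The point holds in a limited form. Table 2 sets a capture schedule for exacerbations that differs by arm, and no common source is named for patients who stop attending. With the planned 20% loss, about 85% of control person-months are captured against 89% in the app arm. This gives an apparent rate ratio of about 1.05 against the app if raw counts are compared (1.02 at 10% loss, 1.08 at 30%).

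Those figures rest on uniform leaving times, equal loss, a constant rate, complete recall at visits and no use of the record review. The bias is small and is demonstrated only for events before leaving. Its size and direction after leaving cannot be derived from the documents.

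Exacerbations are a secondary variable. ACT, the main variable, comes from a questionnaire and cannot be recovered from records. The sample size is unaffected.

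**What to change.** Amend Table 2 and Procedure and instruments as follows.

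- Name the nurse's review of clinical records, with the electronic medication history, as the source of exacerbations for the between-arm comparison.
- Write one rule for which record entries count, and apply it on one schedule in both arms. Staff know the allocation, and the reviewing nurse also monitors the app patients, so the rule should leave little to judgement.
- State that stopping visits or the app does not end this review. It continues to 52 weeks for every randomised patient unless consent to use of records is withdrawn.
- Keep the monthly app reports for their present use in patient management or as supplementary data, outside the between-arm count.

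The cost is an amendment, consent wording and continued chart review for about 22 patients, by a nurse who already reviews all records. If that review does not yet extract exacerbations, a short form for all 108 patients is also needed.

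One downside remains. Events treated outside the accessible records will be missed, possibly not equally by arm, because the app section allows treatment to be adjusted without a visit. Any such limit of the records should be reported with the result.

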### Calculation of the sample

In order to calculate the sample size, a screening of 60 patients seen in the pneumology unit of the center was made with the ACT questionnaire, in order to learn the degree of current control of the asthma of those patients.

With a CI of 95% and a standard deviation of 4.95, the average ACT score of the patients seen in our center was 18.43 ± 1.25. The calculation of the sample size was based upon the established aims. We used the Granmo 7.12 program for two independent averages, accepting an alpha risk of 0.05 and a beta risk of 0.2 in bilateral contrast. Some 54 subjects were determined to be needed for each group in order to detect a difference equal to or greater than 3 units in the ACT questionnaire [16, 17]. We assumed a common standard deviation of 4.95 (obtained by screening in our center) and calculated a rate of loss in follow-up of 20%.

### Sampling technique

The patients will be included in the study by means of accidental probabilistic sampling. Assignment of the intervention to be carried out will be randomly made, according to a randomization grid designed using the software of random.org [18].

### Variables

The main variable of the study will be ACT. Evaluation will be made of the participants in both groups, at the beginning of follow-up, at 6 months, and at 12 months. The results obtained will be compared. In addition, sociodemographic variables will be collected, such as age, sex, education level, and experience in the use of mobile applications. The study variables are detailed in Table 2.

**Table 2 Tab2:** Study variables

Variable	Description	When will it be used?
**Asthma Control Test (ACT)**	ACT is a 5-item questionnaire that assesses the level of control of asthma symptoms during the previous 4 weeks [19].	CG at each visit (v1, v2, v3) IG once a month (using the ESTOI app) and at each visit of the study (V1, V2, V3)
**Test of the Adherence to Inhalers (TAI)**	TAI is a 12-item questionnaire that assesses adherence to inhalers for patients with Asthma or COPD [20].	CG at each visit (v1, v2, v3) IG once a month (using the ESTOI app) and at each visit of the study (V1, V2, V3)
**Asthma Quality of Life Questionnaire (AQLQ)**	AQLQ is a 32-item questionnaire that assesses the quality of life of patients with asthma. Covers 4 dimensions (breathlessness, mood, social limitation and worrying) [21].	Both groups (IG and CG) at each visit (V1, V2, V3)
**The Hospital Anxiety and Depression Scale (HADS)**	HADS is a questionnaire for detecting affective disorders in hospital settings with outpatients. Is frequently used to evaluate populations with chronic diseases [22].	Both groups (IG and CG) at each visit (V1, V2, V3)
**Blood eosinophil count**	Eosinophils are actively involved in diseases caused by parasites and in allergic reactions. In the case of asthma, having eosinophils in range is usually an indicator of good control [4].	Both groups (IG and CG) at V1 and V3
**Immunoglobulin E (IgE)**	IgE is an antibody involved in airway inflammation and allergic reactions. It plays an essential role in modulating severity as a direct association between IgE concentrations and increased disease severity, bronchial hyperresponsiveness and reduced lung performance [4].	Both groups (IG and CG) at V1 and V3
**Exacerbation**	In asthma an exacerbation is considered a worsening of asthma symptoms that requires medical intervention and has at least 1 of the following 3 elements listed below for at least 2 consecutive days: Worsening of asthma signs/symptoms (dyspnea, wheezing, nocturnal awakenings, or chest tightness), increased use of rescue medication or deterioration of lung function [1].	CG at each visit (v1, v2, v3) IG once a month (using the ESTOI app) and at each visit of the study (V1, V2, V3)
**Peak Expiratory Flow (PEF)**	PEF is the highest airflow achieved in a forced expiration after an also forced inspiration, measured using a Peak Flow Meter. It is used as a predictor of airway obstruction [23].	Both groups (IG and CG) once a week (using the ESTOI app in case of IG) and at each visit of the study (V1, V2, V3)
**Forced vital capacity (FVC)**	FVC is the total volume of air that can be exhaled during a maximum effort of forced expiration without a time limit [24].	Both groups (IG and CG) at each visit (V1, V2, V3)
**Forced expiratory volume in one second (FEV1)**	FEV1 is the volume of air exhaled in the first second under force after a maximal inhalation [24].	Both groups (IG and CG) at each visit (V1, V2, V3)
**Bronchodilator Responsiveness (BDR)**	BDR determines the degree of airflow improvement after the administration of a Beta-2 adrenergic agonist. The test is considered positive when there is an increase from baseline values of FEV1 by at least 12% and 200 mL [24].	Both groups (IG and CG) at each visit (V1, V2, V3)
**Fractional exhaled nitric oxide (FeNO)**	FeNO is a useful and noninvasive biomarker for eosinophilic airway inflammation, particularly in asthma [25].	Both groups (IG and CG) at each visit (V1, V2, V3)

*CG* Control group, *IG* Intervention group

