**Fig. 1 Fig1:**
[figure not shown]
Flow chart CG: Control group; IG: Intervention group; BDR: Bronchodilator responsiveness

At the first visit, all of the participants will be seen by the out-patient pneumology unit for classification of their asthma, renewal of their inhalers, and preparation of orders for complementary tests. Following this, the control group will receive instructions provided by a nurse specialized in asthma concerning the illness, the treatment to follow, signs to watch out for, plan of action, and a review of the triggers of the illness. Meanwhile, the patients from the intervention group, in addition to this instruction, will also be included in the database of the ESTOI application and will be provided access to the patient homepage, where they may find all the information needed for the management of their asthma. Both groups will be provided with a Peak Flow device and will receive instruction on how to use it and record the results in a diary.

At the conclusion of the first visit, all of the participants will be given an appointment for a second visit as well as a contact phone number to resolve any questions that may arise.

At the conclusion of the third visit, the intervention group will complete a questionnaire to determine their satisfaction with the app that they used.

All of the relevant data from the study will be collected in the case report form of each patient for subsequent analysis. The case report forms will be housed in the medical center in a locked room to which only the research team will have access.

At each of the three visits in the study, the nurse specialized in asthma will be responsible for compiling the study questionnaires (ACT, TAI, AQLQ, and HADS) of all the patients, reviewing the records of withdrawal from medication, carrying out a FeNO test, doing spirometry with bronchodilator, ordering bloodwork, and making on-site PEF measurement. All of the data will be duly recorded in the case report forms.

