### ESTOI application for the management of asthmatic patients

The mobile application ESTOI, created and managed by the research team of this study, is designed to provide, in a personalized manner, all of the tools normally used in a hospital for the management and control of asthma. ESTOI has a number of components that may be managed and modified by the researchers in response to the needs of each patient. It is available for both Android and IOS devices.

In the first component, ‘CONTROL OF SYMPTOMS’, the participants respond to questions about their health that are designed in a personalized manner in order to learn of their current asthma state. Each month the ACT, TAI, number of exacerbations, and weight will be recorded, as well as, depending on the case, data on the control of symptoms of rhinitis, nasal polyposis, RGE, allergies, and smoking habit, if any. Depending on the results obtained from the questionnaire, the patient will be given recommendations or alerts in accordance with the seriousness of their situation, and the application will automatically alert the medical team when a serious worsening in control of the illness is detected, so as to allow for management of the situation and avoidance of future risk.

In the second component, ‘HEALTH RECOMMENDATIONS’, all of the information that the patient needs to manage the pathology is shown, including how to control it and what to do in the event of a worsening of the symptoms. The recommendations that appear in this component will depend on the patient’s state and comorbidities; only information appropriate to the current state of the patient will be available to him or her.

In the third component, ‘YOUR TREATMENT’, appears up-to-date, personalized information concerning current medication used by the patient to treat asthma, the dosage and times to take the medication, and, in the case of inhalers and biological therapy, a video explaining how they are to be administered. This component also includes the plan of action, showing the medication to be taken by the patient in the event of a worsening of the asthma, as well as in the event of an emergency. Both the treatment and the plan of action will be reviewed and modified, if necessary, at each patient visit to pneumology.

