In the fourth component, ‘PEAK FLOW’, the patient can record the measurements made using the Peak Flow Meter at home. The peak flow is calculated automatically in order to reveal whether there have been significant changes in the values for pulmonary function, so that treatment can be modified and adjusted to current needs without the need for the patient to visit a medical center.

The fifth component, ‘NUTRITIONAL PLAN’, provides a guide to daily foods so that the individual may adapt the tools and advice to his or her needs.

The sixth and final component, ‘MESSAGING’, provides for two-way communication between the participants and the members of the specialized asthma medical team, allowing for additional information to be provided and for questions to be answered.

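### The exacerbation count depends on access to medical care, which the app changes in one arm only, and it is collected more often in that arm

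*Protocol article*

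**What the plan says.** **Definition.** In the Variables section of the protocol article, the Exacerbation row of Table 2 requires the following: "worsening of asthma symptoms that requires medical intervention and has at least 1 of the following 3 elements listed below for at least 2 consecutive" (counted in days). The three elements are alternatives: worse signs or symptoms, more rescue use, or worse lung function.

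**Collection.** The same row gives the schedule as "CG at each visit (v1, v2, v3) IG once a month (using the ESTOI app) and at each visit of the study (V1, V2, V3"). The Variables section places the assessments in both groups at the start, 6 months and 12 months.

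**What the app adds.** The section on the ESTOI application says "the application will automatically alert the medical team when a serious worsening in control of the illness is detected". Peak flow entries are processed "so that treatment can be modified and adjusted to current needs without the need for the patient to visit a medical center". A messaging component links the patient with the asthma team.

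**What both arms receive.** Procedure and instruments gives both groups nurse teaching, including an action plan, and a telephone number for questions. It also states: "Both groups will be provided with a Peak Flow device and will receive instruction on how to use it and record the results in a" (the record is a diary). Peak flow is scheduled for "Both groups (IG and CG) once a week (using the ESTOI app in case of IG) and at each visit".

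**Masking.** Under Limitations, the article states that the research team and clinical staff know each patient's group throughout, and that this could affect how results are evaluated.

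**Role of the outcome.** ACT is the main variable. The number of exacerbations is a listed secondary variable. It is also one of the measures of asthma control named under Limitations and a candidate factor in the regression models under Analysis of the data.

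**The concern.** One condition for counting an event is that medical intervention is required, and the treatment under test supplies easier access to medical intervention. The condition can be read in two ways, and neither is neutral between arms:

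- **Intervention received.** The app provides routes to it (alert, chat, remote change of treatment) that controls do not have.
- **Intervention needed.** Staff who know the allocation judge the need, and they have monthly app data for one arm only.

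The article does not say whether an alert, a chat exchange or a remote treatment change qualifies.

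The collection schedule adds to this. Controls must recall about six months at a time, while app patients are also asked every month. Both features can make the counts differ when the disease does not, or hide a difference that is real.

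**Working it through.** **1. The plan's own figure.** The only related calculation in the article is the ACT sample size. The inputs under Calculation of the sample are: difference 3, SD 4.95, two-sided alpha 0.05, beta 0.2, loss 20%.

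- n per arm = 2 × [4.95 × (1.960 + 0.842) / 3]² = 42.7, rounded up to 43.
- 43 / 0.80 = 53.75, rounded up to 54; 2 × 54 = 108.

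This reproduces the article's 54 and 108. The present point does not touch it.

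**2. Routes to a counted event, side by side.**

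| | Control | Intervention |
|---|---|---|
| Action plan, telephone number | yes | yes |
| Peak flow meter, weekly reading | yes, diary | yes, app |
| Automatic alert to the team | no | yes |
| Two-way messaging | no | yes |
| Treatment change from app peak flow, without a visit | no | yes |
| Occasions of asking after baseline | V2, V3 (2) | about 12 monthly entries plus V2, V3 (about 14) |

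The last four rows differ by arm. Asking both arms only at V2 and V3 would remove the last difference but not the three above it.

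**3. What unequal counting could do.** The article gives no exacerbation rates, so every input here is assumed except n = 43 per arm (step 1, after 20% loss) and one year of follow-up. Let the true rate of worsenings λ be the same in both arms, and let shares p_C and p_I be counted.

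- Counted rate ratio = p_I / p_C.
- SE of the log ratio (Poisson) = √[1/(43·λ·p_C) + 1/(43·λ·p_I)].
- With d = |log ratio| / SE, chance of p < 0.05 = Φ(d − 1.96) + Φ(−d − 1.96).

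Example with λ = 1, p_C = 0.50, p_I = 0.75: the expected counts are 21.5 and 32.25, SE = 0.278, d = 0.405/0.278 = 1.46, and the chance is 0.31.

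| p_C | p_I | Counted ratio | Chance, λ = 0.5 | λ = 1 | λ = 2 |
|---|---|---|---|---|---|
| 0.50 | 0.50 | 1.00 | 0.05 | 0.05 | 0.05 |
| 0.50 | 0.60 | 1.20 | 0.07 | 0.10 | 0.14 |
| 0.50 | 0.75 | 1.50 | 0.18 | 0.31 | 0.54 |
| 0.75 | 0.50 | 0.67 | 0.18 | 0.31 | 0.54 |

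The last row shows that the distortion can favour the app just as easily. If counts vary more than Poisson, the SE is larger and, provided the test allows for it, these chances fall. The ratios do not change.

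**4. The lung-function element.** Readings seven days apart never fall on consecutive days. On a daily grid, a 2-day fall contains any reading with probability 2/7 = 0.29. Two readings within one episode need at least 8 days (probability 1/7 = 0.14 at 8 days, 3/7 = 0.43 at 10 days, 1.0 at 14 days). At the planned frequency this element cannot be shown as defined. These figures are the same in both arms.

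**The case against.** **The definition speaks of need, not receipt.** This is fair as a reading of the words, and the article does not equate the two. It does not remove the problem, because need is judged by unmasked staff with more information on one arm.

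**A condensed article leaves detail to the full protocol, and the definition is attributed to a guideline.** A rule on which contacts qualify may exist elsewhere, and its absence alone would be no finding. The care-dependent condition, the one-sided access and the unequal schedule are all stated in the article.

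**The outcome is secondary, and the authors already concede that unmasked staff may influence evaluation.** Both are true, and they limit the severity. The concession does not mention the definition or the schedule.

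A reader might infer more than the documents support:

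- **That the app also distorts the 2-day rule.** The rule is identical in both arms. If earlier treatment brings an episode below two days, that is arguably a real benefit.
- **That weekly peak flow makes the counts differ between arms.** The schedule is common to both arms, lung function is one of three alternatives, and more frequent self-measurement is not excluded. This is a weakness of measurement, not between-arm bias.
- **That a real 30% reduction would vanish.** With 50% of worsenings counted in controls and 70% in the app arm, a true ratio of 0.70 becomes 0.70 × 0.70/0.50 = 0.98. That is one assumed pair of shares. With 40–60% in controls and 60–80% in the app arm the result runs from 0.70 × 0.60/0.60 = 0.70 (no distortion) to 0.70 × 0.80/0.40 = 1.40, and only the upward direction is modelled.

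**Conclusion.** The concern holds in a limited form. The written definition is the same in both arms, but its application and ascertainment can differ: one condition depends on care that only the app arm receives more easily, staff are unmasked, and one arm is asked monthly. It would go too far to say that the two arms count different events, or that the bias has a known sign.

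No fixed size can be computed. The illustrative ratios of 1.2 to 1.5, or 0.67, rest wholly on assumed shares and rates. The problem affects a non-primary outcome and leaves the ACT comparison and its sample size intact. It should be corrected before a between-arm difference in exacerbations, or the lack of one, is read as an effect on disease.

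**What to change.** 1. **Add a severe exacerbation count for the between-arm comparison:** systemic corticosteroid course for asthma, emergency department visit or admission, whatever the duration. Take it from the same health-record source, over the same period, with criteria fixed in advance for both arms. Report emergency visits and admissions separately as the component least affected by the app.
2. **Keep the present definition as a supporting outcome.** Compare arms only on data collected the same way at V2 and V3. The monthly app entries can describe the intervention arm.
3. **State one rule for remote contact, by app or telephone, and apply it to both arms.** Excluding app contact alone would create a new imbalance, because a control patient whose treatment was changed by telephone would still count.
4. **Note that the lung-function element cannot be shown on consecutive days from weekly readings.**

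The cost is protocol wording and a case report form item. The telemedicine nurse already reviews the records of all patients but also manages the app patients, so classification from extracts with the arm masked is preferable. The downside is fewer events and less precision for this secondary outcome. Corticosteroid courses can also follow remote contact, so the new count reduces the dependence on access to care but does not remove it.
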